### Study design

The research design for the evaluation of the orientation programme is a pre- and post-test, clustered staggered design with T1 (target *n* = 15) and T2 (target *n* = 15) groups. T1 will participate in the orientation programme initially, while T2 will participate in a subsequent orientation. The peer educator capacity of tuakana will be assessed at three stages: pre-intervention, post-intervention for the T1 group, and post-intervention of the T2 group. After the orientation programme, each tuakana will talk with each teina at least three times to address the specific life-transitions of teina. Teina also will complete three evaluations with variations for the two groups: (a) T1: pre-intervention, approximately four months post-intervention, and then four months after the second evaluation; (b) T2: pre-intervention, approximately four months after initial survey, and then four months post-intervention. This staggered approach was approved by the Board Advisory Group during the original proposal as fitting the mission of the organisation and the needs of kaumātua. Consistent with Kaupapa Māori principles, withholding an intervention from participants is not ethical. Thus, the research design enables a rigorous comparison of the orientation programme whilst ensuring that all teina receive the intervention. Further, the use of a staggered design is a strong, and pragmatic design for interventions in the health service sector [56]. Figure 1 illustrates the staggered research design. The project is registered with the Australia New Zealand Clinical Trial Registry (ACTRN12617001396314).

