### Intervention-related measures

Several measures of mana motuhake will be directly related to the intervention. Based on a guideline for creating self-efficacy scales, five items were created for this study to assess the perceived self-efficacy of tuakana in relation to their ability to fulfil the role of tuakana [69]. Using three items created for this study and one item from a previous study [70], the perceived effectiveness of the orientation programme will be determined by the tuakana. For both tuakana and teina, we will include three items created for this study about the perceived satisfaction of the interaction with each other in terms of the time spent, interaction, and advice provided.

Additional measures about the intervention will relate to the conversations between tuakana and teina. Tuakana will have at least three conversations with each teina over a two-three month period. Checklists will be provided to the tuakana to help structure their conversations with teina around specific aspects to be covered in the orientation programme. The conversations will be audio recorded with the permission of the participants. A research team member will code the conversations to check the fidelity of the conversations to the orientation programme. The coding sheet will be a similar checklist given to the tuakana. Coders will be trained by one of the senior research team members on the coding procedures and rules. A separate researcher will code approximately 10% of the interactions to establish inter-coder reliability prior to completion of the primary coding.

The intervention will enable participants to talk about their transitions and enhance meaning about them. There is a chance that T1 participants will talk with T2 participants in the other group; this is understandable and not something we wish to control. We will measure whether participants talk to other kaumātua at RKCT about the project/life transitions and used these measures as confounders in the analyses. These measures mitigate impact on research design.

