#### Intervention evaluation

The purpose of the analysis is to determine whether the peer-educator model results in changes to hauora and mana motukahe between pre-test and post-test. The analysis will compare the two groups and identify if there are intervening variables that explain differential patterns in the changes in the dependent variables*.* The dependent variables are mana motuhake and haurora. The independent variables are the time receiving the orientation programme (T1/T2) and the three time periods (pre-intervention, post T1-intervention, post T2-intervention). Potential intervening variables that will be controlled for include characteristics about the conversations, characteristics of the tuakana/teina, and whether participants talked with each other during the intervention.

The quantitative data are at three levels—repeated measures of variables (three-time periods), individual characteristics of the teina/tuakana, and characteristics about the conversations with the tuakana. The inclusion of multiple levels requires the use of multilevel statistical models to account for clustering. The analysis will account for the nature of the change in the variables along with characteristics about the teina and tuakana that may influence those changes.

Further, we will determine estimates of cost effectiveness using incremental cost effectiveness analysis (ICEA) [75, 76]. Cost-effectiveness analysis involves estimating the cost per unit improvement in the primary outcome variable. We will use HRQOL as an outcome measure for the ICEA [77]. ICEA involves estimating the ratio of the increase in the outcome variable (as measured by the estimated effect size from the intervention trial) to the estimated average cost per participant of the programme (the incremental cost-effectiveness ratio, or ICER). This calculation assumes that the cost of the status quo (no intervention) is zero. ICER is a common measure used in the evaluation of cost-effectiveness of health interventions [78, 79]. The ICER can then be compared with an explicit target (or costs of alternatives) to determine cost effectiveness.

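### The analysis meant to show whether the programme works controls for events that follow assignment, and the claim that this mitigates contamination does not hold

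*Protocol article*

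**What the plan says.** Intervention evaluation states the aim: "The purpose of the analysis is to determine whether the peer-educator model results in changes to hauora" (and mana motuhake). The means is a comparison of T1 and T2 over three time periods in a multilevel model. The same paragraph adds a second, explanatory aim, to "identify if there are intervening variables that explain differential patterns in the changes in the dependent variables". It then commits to adjustment: "Potential intervening variables that will be controlled for include characteristics about the conversations, characteristics of the tuakana/teina, and whether participants talked with each other", the last item referring to the intervention period.

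Intervention-related measures deals with contamination. It accepts that "There is a chance that T1 participants will talk with T2 participants in the other group" and does not try to prevent this. Participants are asked whether they talk with other kaumātua about the project or life transitions, and the text says the plan "used these measures as confounders in the analyses. These measures mitigate impact on research design".

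Study design shows what the conversations are: "After the orientation programme, each tuakana will talk with each teina at least three times to address the specific life-transitions of teina". It also places T2's second survey about four months after its first, before T2 receives the intervention.

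**The concern.** A confounder is a common cause of group membership and outcome. Two of the three kinds of variable listed cannot be that, because they arise after assignment. Conversation characteristics describe the intervention as delivered. Talking about the project happens while the intervention runs, is plausibly increased by it, and is how T2 might be exposed early. The third kind, tuakana and teina characteristics, can be baseline variables. Adjusting for those is sound, the more so because Sample and recruitment allows convenience assignment.

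At stake is the meaning of the main estimate. With post-assignment variables in the model, the T1/T2 coefficient need not be the effect of being offered the programme. The contamination sentence also tells the reader that a known threat has been handled when it has not. The trial's estimated effect size feeds the cost-effectiveness ratio, so any distortion carries through to it.

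**Working it through.** **The plan's own figure.** Sample and recruitment and Study design give 15 + 15 tuakana, 6 teina each, ICC 0.10, alpha .05, d = .55 and power .80. Design effect = 1 + (6 − 1) × 0.10 = 1.5, so 90/1.5 = 60 effective teina per group. Non-centrality = 0.55/√[4 × (0.10 + 0.90/6)/30] = 0.55/0.183 = 3.01. With 28 df, two-sided, power is 0.83 (0.785 with five teina per tuakana). Six is therefore the smallest cluster size that reaches .80. The figure is slightly conservative and is no finding; 0.55 serves below as the reference effect.

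**Timing.**

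| Variable | When it arises | State at the second survey |
|---|---|---|
| Baseline tuakana/teina characteristics | Before assignment | Known in both groups |
| Conversation characteristics | After orientation | T1 has them; T2 has had no conversations |
| Talking with others | During the intervention | May be affected by group |

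The second survey gives the only contrast with an untreated group, and there the last two rows follow assignment.

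**Conversations, collinearity (assumed coding).** Suppose the covariate is a count, 0 for T2 and 3 plus a Poisson excess with mean λ for T1. In large samples VIF = 1 + (3 + λ)²/(2λ).
- λ = 1: 1 + 16/2 = 9.
- λ = 0.25: 1 + 10.56/0.5 = 22.1.

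Simulation with 90 per group gives 9.3 and 23.7, so the SE is 3.1 to 4.9 times larger.

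**Conversations, bias (assumed model).** Let T1 dose be 3 + 0.5u + 0.8e, with u an unmeasured trait, and T2 dose be 0. Let a share a of the effect run through dose, and let u affect the outcome with coefficient c. T2 dose does not vary, so the dose slope comes from T1 alone, and the adjusted group effect is (1 − a) × 0.55 − 3 × c × 0.5/(0.25 + 0.64).
- c = 0: 0.55 at a = 0; 0.275 at a = 0.5 (simulated 0.28); 0 at a = 1.
- c = 0.4: the last term is 0.674, giving −0.12, −0.40 and −0.67.

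**Talking, no spillover (assumed model).** Let fractions p₁ and p₂ = 1 − p₁ of T1 and T2 report talking, let sociability correlate r with outcome, and let it load ℓ on the propensity to talk. Adjusted effect = 0.55 − r × [ℓφ(z)/(p₁(1 − p₁))] × (p₁ − p₂), where z is the normal quantile of p₁ and φ is the normal density.
- 70% v 30%, r = 0.3, ℓ = 0.7: 0.7 × 0.348/0.21 = 1.16; 0.55 − 1.16 × 0.3 × 0.4 = 0.41.
- 80% v 20%, r = 0.5, ℓ = 0.7: 0.7 × 0.280/0.16 = 1.225; 0.55 − 1.225 × 0.5 × 0.6 = 0.18.
- The same two cases with ℓ = 0.2 and 0.3 respectively: 0.51 and 0.39.

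**Talking, with spillover (simulated, assumed inputs).** T2 teina who talk gain 50% or 100% of the effect. Talking follows a logistic model with intercept −1, 1.2 for T1 and 0.8 per SD of sociability.

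| Spillover | Sociability effect on outcome | Unadjusted | Adjusted for talk |
|---|---|---|---|
| 50% | 0 | 0.47 | 0.44 |
| 50% | 0.4 | 0.47 | 0.37 |
| 100% | 0 | 0.38 | 0.32 |
| 100% | 0.4 | 0.39 | 0.26 |

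Contamination dilutes the unadjusted estimate, and in these settings adjustment moves it further from 0.55. The reason is that talking raises the outcome in T2, which gives a positive pooled slope. T1 talks more, so the adjustment takes away from T1.

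**A coding that changes nothing.** If talk enters only as a time-constant main effect γTᵢ, it cancels from each teina's change score. With complete data the group-by-time effect is then the same with or without it. A three-wave simulation gave 0.537 both ways.

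**The case against.** The strongest reply is that the section has two aims. It speaks of potential intervening variables, which is the language of mediation, and a journal article need not spell out the order of models. Conversation characteristics are also listed as a data level separate from the repeated measures. T2 teina have them by the end of the study, so they need not duplicate the group variable.

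Much of this stands, and it limits what can be claimed. Three stronger readings are tempting.
- A reader might infer that the plan calls conversation characteristics confounders. It does not; that label is given only to the talk measures, and the evaluation section calls the whole list intervening.
- A reader might infer that the group effect becomes almost inestimable, or that the untreated T2 comparison drops out. Both need a coding (zeros or blanks for T2) that the article does not state.
- A reader might infer a known bias towards zero. The documents give no talking rates, no link between sociability and talking, and no mediated share. The larger attenuations need a strong link (ℓ about 0.7).

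What does not stand is the defence of the adjustment itself. The explanatory aim justifies a secondary process analysis. It does not justify controlling for these variables in the analysis that is to establish the effect, and no separate total-effect model is described. Nor does it rescue the statement that measuring and adjusting for talk mitigates contamination. Under the harmless coding the adjustment leaves the dilution untouched.

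**Conclusion.** The point holds as a should-fix. The article commits the effectiveness analysis to controlling for post-assignment variables and wrongly presents adjustment for talking as a remedy for contamination. That conclusion rests on the timing and roles the article itself gives, not on any simulation.

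The size is not determined. The VIF of about 9 to 24, the 0.51 to 0.18 range for talking and the conversation-dose results are conditional illustrations. With no mediation, shared cause or spillover the estimate stays near 0.55, and some codings leave it unchanged. Design and data collection are unaffected.

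**What to change.** In Intervention evaluation, state that the programme effect is the T1/T2-by-time effect from the multilevel model, with T1 v T2 at the second assessment named as the contrast against an untreated group. Adjust only for variables fixed before assignment (baseline tuakana and teina characteristics and the pre-test score) and for clustering by tuakana. Use this estimate for the cost-effectiveness ratio.

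Move conversation and fidelity measures to a labelled secondary dose or mediation analysis. Report talking across groups by group, with a contamination sensitivity analysis.

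In Intervention-related measures, replace the two sentences on confounders and mitigation with a statement that talking between groups may dilute the estimate.

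The cost is wording in the analysis plan. No new data are needed, and the explanatory aim is kept. The drawback is a less favourable statement about contamination.

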### Research aims

We seek to address the mana motuhake of kaumātua, asking: What are the outcomes of a ‘tuakana-teina’ peer-educator model, where kaumātua work with other kaumātua in relation to wellness, social integration/connectedness, engagement, life-enhancement, independence, and, in particular, significant life-transitions? The project has four specific objectives: (a) To develop the capacity of kaumātua as peer educators/supporters and have positive impacts on their sense of purpose and health and wellbeing; (b) To enhance the social and health outcomes for kaumātua receiving the intervention; (c) To determine the cost-effectiveness of the intervention; and (d) To determine whether and how the intervention could be scalable through effective dissemination and implementation processes.

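### The ICER is defined as effect over cost, the reciprocal of the cost per unit of gain that the same paragraph sets out to estimate

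*Protocol article*

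**What the plan says.** Objective (c) under Research aims is "To determine the cost-effectiveness of the intervention". The method is in the last paragraph of Intervention evaluation, which makes these statements in order:

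- The general aim: "Cost-effectiveness analysis involves estimating the cost per unit improvement in the primary outcome variable".
- The outcome: "We will use HRQOL as an outcome measure for the ICEA".
- The definition: "ICEA involves estimating the ratio of the increase in the outcome variable", with that increase taken "as measured by the estimated effect size from the intervention trial", and the ratio formed "to the estimated average cost per participant of the programme (the incremental cost-effectiveness ratio, or ICER").
- The comparator: "This calculation assumes that the cost of the status quo (no intervention) is zero".
- The use: "The ICER can then be compared with an explicit target (or costs of alternatives) to determine cost effectiveness".

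The article gives no programme cost, no target value and no unit for the target. No other section restates or corrects the direction of the ratio.

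**The concern.** The first statement puts cost on top and effect underneath. The definition puts effect on top and cost underneath. Both are offered as the measure for the same objective, and only the second carries the label ICER. The last statement then sets that quantity beside a target or the costs of other options, and the costs of other options are sums of money.

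An analyst who follows the definition literally will report effect per dollar under a name that readers take to mean dollars per unit of effect. The Discussion section says cost-effectiveness estimates will form part of a value proposition shared widely with providers and policy users, so the number is likely to be read by people who did not compute it. What is at stake is the correct reading of one reported ratio and of any benchmark comparison made with it.

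**Working it through.** The article states no ICER, cost or target, so there is no figure to reproduce. The check is on definition, units and direction, followed by an illustration.

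**Inputs**
- Effect E: 0.55, the planning effect size in Sample and recruitment. It is used here only to put a number in. Treating the trial's estimated effect size as standardised in the same way is an assumption. A smaller assumed value of 0.2 is shown for range.
- Cost C per participant: not given. Assumed values are $200, $500 and $1,000.
- Status quo cost: zero, as the article assumes, so incremental cost equals C.

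**Formulas**
- Stated aim: (C − 0) / E, in dollars per unit of effect. Smaller is better.
- ICER as defined: E / C, in units of effect per dollar. Larger is better.

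**Results**

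| Assumed C | E | Aim: C / E | As defined: E / C |
|---|---|---|---|
| $200 | 0.55 | $364 | 0.00275 |
| $500 | 0.55 | $909 | 0.0011 |
| $1,000 | 0.55 | $1,818 | 0.00055 |
| $200 | 0.2 | $1,000 | 0.001 |
| $500 | 0.2 | $2,500 | 0.0004 |
| $1,000 | 0.2 | $5,000 | 0.0002 |

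**Is the cost range reasonable?** The article gives koha of about $45 per event for tuakana and $40 for teina, and at least three conversations per teina. If each conversation counts as one event for both people, conversation koha alone is 3 × (45 + 40) = $255 per teina. Then 255 / 0.55 = $464 per unit of effect, against 0.55 / 255 = 0.0022 as defined. Orientation, staff and other costs would come on top.

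**Direction.** At E = 0.55, compare C = $200 with C = $1,000. Cost per unit of effect favours the cheaper programme ($364 against $1,818). So does the written ratio, if larger is read as better (0.00275 against 0.00055). If the written ratio is instead read by the usual ICER convention, smaller is better, and the dearer programme appears preferable.

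**The case against.** The strongest reply is that this is a slip of wording that the paragraph itself exposes. The opening statement and the reference to the costs of alternatives both point to cost over effect, and an analyst who obtained about 0.001 per dollar would see that it could not be set against a sum of money. The two forms are reciprocals, so nothing is lost. Objective (c) is one of four, the abstract lists only (a) and (b), and the multilevel models do not depend on the ratio. All of that stands, and it limits how serious the point is. It does not remove the contradiction, because the formula attached to the name ICER is still the wrong way up.

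Several stronger readings are tempting, but the document does not support them:

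- A reader might infer that ranking against alternatives is reversed. For positive effects, the two ratios give the same ranking when each is read in its own direction. Reversal needs one ratio to be computed and the other's rule applied.
- A reader might infer that every programme would pass. That needs a target in dollars per unit and a rule that below target means cost-effective. The article states neither a unit nor a direction for its target, so this is a conditional risk.
- A reader might object that the HRQOL items lack utility weights or cannot be compared with per-QALY thresholds. The plan mentions no QALYs, and cost per unit of HRQOL needs no utility weights.
- A reader might treat the use of an effect size as a second error. The article does not say it is standardised, and scaling is commonly left to a fuller analysis plan.

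**Conclusion.** The point holds as an internal contradiction in the definition of the measure for objective (c). The stated aim is cost over effect, and the ICER is defined as effect over cost. Computed as written, the ICER is in effect per dollar with larger better, so it cannot be set against a cost or cost-per-unit benchmark.

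At an assumed $500 per participant and an effect of 0.55, the two versions are 0.0011 per dollar and $909 per unit. Those figures show the difference in scale and direction. They do not measure bias in this trial, and they rest on an assumed cost and on borrowing the planning effect. That a dollar-based benchmark is intended is an inference from the stated aim and from the mention of alternatives' costs.

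The correction is at the level of wording, affects one of four objectives, and leaves the effectiveness analyses as they are. It should be made before any ICER is calculated.

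**What to change.** Replace the defining sentence with one to this effect: the ICER is the average programme cost per participant, minus the status quo cost (assumed to be zero), divided by the estimated increase in HRQOL attributable to the intervention.

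Amend the comparison sentence so that the ICER is compared only with a target, or with alternatives, expressed as cost per unit of the same HRQOL measure.

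If the sponsor prefers effect per dollar, the other coherent course is to keep that ratio under a different name and state that larger is better, with benchmarks in the same unit.

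The cost is a sentence or two of text. No new data, participants or analyses are needed.

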### Sample and recruitment

Tuakana will be purposively sampled to include kaumātua with effective peer educator attributes. The advisory groups considered the relevant peer educator attributes for ageing research [41] and attributes within Te Ao Māori such as mana, pono, aroha and tika [6, 19]. Tuakana will receive koha (an offering) towards their participation in the programme, conversations with teina, and data collection over the duration of the project (approximately $45/event).

The project will have a target of 180 teina participants randomly selected from the RKCT client base of approximately 600 kaumātua that affiliate to various iwi (tribes). Tuakana will be removed from the sampling frame. Teina will be assigned to a tuakana with matched biological sex. The only exclusion criteria is ethnicity (i.e., not being Māori). Decline and retention rates (including reasons such as withdrawal and passing away) will be tracked. Teina will receive koha as a contribution towards their participation in conversations and data collection (approximately $40/event). Tuakana and teina will be assigned to T1 and T2 groups ideally using random assignment although convenience assignment will be accommodated and tracked (e.g., when they were able to participate or to match tuakana/teina).

The sample sizes of tuakana and teina were determined by a balance of resources and statistical power to determine the optimal design. We conducted power and sample size estimates based on the research design [57] and confirmed with the ‘od.exe’ software package [58]. The following assumptions were made: (a) probability value = .05; and (b) rho (intra-class correlation) = .10. Six teina for each tuakana results in power of .80 with a medium effect size (d = .55). A medium effect size was chosen given prior research on the impact of elder peer educators on self-rated health and related wellbeing outcomes [37, 38].

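### The cost-effectiveness step for objective (c) compares a point-estimate ratio with a target, uses no measure of uncertainty, and describes the ratio in two opposite directions

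*Protocol article*

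**What the plan says.** The Research aims section of the protocol article lists as objective (c): "To determine the cost-effectiveness of the intervention". The Intervention evaluation section of the Data analysis plan sets out how:

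- The general description is "Cost-effectiveness analysis involves estimating the cost per unit improvement in the primary outcome variable", that is, cost divided by effect.
- The outcome is named: "We will use HRQOL as an outcome measure for the ICEA".
- The ratio is then defined from its two parts: "ICEA involves estimating the ratio of the increase in the outcome variable (as measured by the estimated effect size from the intervention trial" and "to the estimated average cost per participant of the programme (the incremental cost-effectiveness ratio, or ICER". That is effect divided by cost, the inverse of the general description.
- The comparator is costed at nil: "This calculation assumes that the cost of the status quo (no intervention) is zero". The incremental cost is therefore the programme cost, which is positive.
- The closing step is "The ICER can then be compared with an explicit target (or costs of alternatives) to determine cost effectiveness".

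No standard error or interval enters this step. The paragraph just before it commits the outcome analysis to multilevel models that account for clustering, so a standard error for the effect will be available.

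**The concern.** The closing step is worded as the one that settles objective (c), and each input to it is a single number. A small positive estimate that arose by chance is treated as if it were known exactly. The result can therefore be favourable although the trial has not shown that HRQOL improved.

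The two directions add a second difficulty. On an effect-to-cost scale, favourable means above the target. On a cost-per-unit scale, it means below. Until the section settles on one, a reader cannot tell which inequality applies or how an estimate at or below zero is to be read.

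The Discussion says that estimates of cost-effectiveness will form part of a value proposition shared widely near the end of the project, and that the research is meant to contribute to government strategy. A cost-effectiveness statement with no indication of its precision would carry more weight there than the data support.

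**Working it through.** **Inputs.** Study design section: 15 tuakana per group. Sample and recruitment section: 180 teina (90 per group), six per tuakana, "a) probability value = .05; and (b) rho (intra-class correlation) = .10", power .80 at d = .55. Two-sided testing is assumed, because sidedness is not stated.

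**The plan's own figure.** With J = 30 clusters of n = 6, the noncentrality is J·d² / (4·(ρ + (1 − ρ)/n)) = 30 × 0.3025 / (4 × 0.25) = 9.075. The F test on 1 and 28 degrees of freedom then has power .828, and the normal approximation gives .854. If d is expressed in within-cluster SDs (0.55 × √0.9 on the total-SD scale), the figures are .788 and .815. The stated .80 is therefore reproduced to within two points on the within-cluster reading and is slightly conservative on the other. It is not in dispute.

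**Standard error of the effect.** The design effect is 1 + (6 − 1) × 0.10 = 1.5. SE = √(2 × 1.5 / 90) = 0.183 SD. This is for one unadjusted comparison of the two groups with no dropout.

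**Chance of a favourable result when the true effect is zero.** Treat the cost C as fixed and positive. Let e* be the effect, in SD, at which the ratio exactly meets the target. On the effect-to-cost scale, or on cost per unit with a positive estimate required, the step is favourable when the estimate exceeds e*. The probability is 1 − Φ(e*/SE). The values of e* are assumptions. The outer columns show an assumed range for SE.

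| e* (SD) | SE 0.12 | SE 0.183 | SE 0.22 |
|---|---|---|---|
| 0.05 | .34 | .39 | .41 |
| 0.10 | .20 | .29 | .33 |
| 0.20 | .05 | .14 | .18 |
| 0.30 | .01 | .05 | .09 |

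The probability approaches .50 only as e* approaches zero.

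**What taking account of uncertainty changes.** If the lower 97.5% bound of the effect had to reach e*, the probability would be 1 − Φ(e*/SE + 1.96). That is .006 at e* = 0.10 (against .29) and .001 at e* = 0.20 (against .14).

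**Precision at the planned effect.** 0.55 ± 1.96 × 0.183 gives 0.19 to 0.91. Cost per unit is C divided by the effect, so its range is 0.908 / 0.192 = 4.7-fold. An estimate of 0.30 has an interval of −0.06 to 0.66, yet it would pass at any e* below 0.30.

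**The case against.** The strongest reply is that this is a condensed article. Intervals, the target value and the handling of a null effect usually belong in the full protocol or analysis plan, and their absence here is not an error. The closing sentence says the ratio can be compared, offers two kinds of comparator and sets no target, so it may be explanation rather than a fixed rule. The Discussion also makes dissemination conditional on the model being effective, so a favourable ratio alone would not trigger scaling. The standard error above is not that of the planned repeated-measures model, and the break-even effects are assumed. Finally, net benefit is one accepted presentation among several and needs a money value per HRQOL unit.

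Much of this stands. It limits the consequence and makes the percentages illustrative. It does not remove the point, because the section does state the comparison by which cost-effectiveness is to be judged, and that comparison uses point values. Nor does net benefit need anything extra: comparing a ratio with a target already requires a cost and a value per unit.

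A reader might go further and infer that an ineffective programme would be called cost-effective half the time or more. On a cost-per-unit scale a negative estimate gives a negative ratio, which lies below any positive target. Counting those as passes adds .50 to the probabilities at SE 0.183, giving about 89%, 79%, 64% and 55%. The documents do not support this. The ICER is defined there as effect to cost, where a negative effect fails every positive target. Nothing says that a negative ratio counts as a pass. Those rates are a conditional worst case.

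**Conclusion.** The point holds in a limited form. The stated comparison takes no account of sampling error. With no true effect it would be favourable in roughly 5% to 39% of trials for break-even effects between 0.30 and 0.05 SD, and in fewer than half for any positive target on the ratio as defined. Even at the effect the trial was planned for, cost per unit is known only to within a 4.7-fold range. These sizes rest on the planning inputs, an unadjusted standard error, a fixed cost and assumed break-even values.

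The two directions of the ratio are a plain inconsistency within one paragraph and need no assumption. The point is worth correcting, but it does not affect the outcome analysis of hauora and mana motuhake.

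**What to change.** In the Intervention evaluation section:

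1. State the ratio in one direction throughout.
2. Base the cost-effectiveness statement on incremental net benefit: target value per HRQOL unit × estimated effect − incremental cost per participant. Take the effect and its standard error from the multilevel model clustered on tuakana.
3. Report net benefit with a 95% interval, and the probability that it is positive, over a range of target values.
4. Report the ICER alongside as a descriptive figure.

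The point estimate of net benefit is positive exactly when the estimated effect exceeds e*, so the gain comes from the interval and the probability. Net benefit also removes the sign ambiguity: with a positive cost and target value, an effect at or below zero always gives a negative net benefit.

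The cost is a change of wording and a small extra analysis of data already planned. The statement on objective (c) will be less clear-cut.
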